## Abstract

**Background:**

Participation in physical activity has been found to be beneficial for mental and physical health outcomes among cancer survivors. However, to date no intervention exists specifically to promote physical activity among bladder cancer survivors. In light of this knowledge a home-based exercise intervention was co-created for those recently diagnosed with bladder cancer.

**Aim:**

The aim of the present study, financially supported by Action Bladder Cancer UK [1], is to pilot the home-based exercise intervention tailored specifically for bladder cancer survivors (i.e. from the point of diagnosis) to improve physical and mental health outcomes (during treatment and beyond) in this population.

**Methods:**

This study will use a randomised controlled trial design. Arm one will consists of the 14 week home-based exercise intervention and arm two usual care (15 participants will be randomised to each arm). Baseline data collection will take place shortly after clinical diagnosis of bladder cancer, and follow-up approximately 7 weeks and then again approximately 14 weeks after commencement of the intervention. At each data collection point data will be collected from participants relating to demographics, physical and mental health. Participants will aslo be asked to wear an Actigraph Accelerometer at each data collection point for seven consecutive days. Immediately after baseline data collection participants in the intervention arm will be given the home-based exercise booklet.

**Ethics and dissemination:**

Ethical approval was obtained for the present study via The London- City and East Research Ethics Committee (ID:291676). Results of this study will be disseminated through peer-reviewed publications and scientific presentations.

## Introduction

1

Approximately, 10,000 people are diagnosed with bladder cancer every year and it's the tenth most common cancer in the UK. The condition is more common in older adults, with most new cases diagnosed in people aged 60 and above [2]. Importantly, the survival rate for bladder cancer (when compared to some other cancer types) is good. The general 5-year survival rate for people with bladder cancer is 77%, the overall 10-year survival rate is 70% and the overall 15-year survival rate is 65% [3].

There are many common physical and psychological consequences of cancer and treatment, including fatigue, pain, sleep disturbance, lymphoedema, weight gain, loss of muscle mass, cancer-related distress (e.g. fear of recurrence, financial concerns), anxiety, and depression [4,5]. Furthermore, the majority of people living with and beyond cancer are living with at least one other long-term chronic condition (e.g. hypertension, obesity, mental health conditions) [6]. Treatment for bladder cancer often includes surgery (including Transurethral bladder tumour resection, Radical cystectomy and lymph node dissection, Urinary diversion [stoma]), but may also include chemotherapy, immunotherapy, and targeted therapy. These treatments result in specific unwanted side effects including for example, mild bleeding and discomfort after surgery, erectile dysfunction, loss of sexual feeling and orgasm, frequent urination, and those with advanced bladder cancer may have been fitted with a uro-stoma [7].

With a high bladder cancer survival rate and thus a relatively large proportion of people living with and beyond bladder cancer [8] it is important to consider health behaviour interventions to improve general health, bladder cancer-specific complications, and general quality of life. One such intervention may include the promotion of physical activity. Indeed, physical activity has been shown to reduce cancer-related fatigue, pain, maintain an adequate weight and muscle mass, reduce levels of distress, anxiety and depression, reduce the risk of erectile dysfunction, and aid in the prevention and maintenance of several other non-communicable diseases [[9], [10], [11]]. In light of this knowledge The Independent Cancer Taskforce recommended that everyone diagnosed with cancer in the UK should have access to the elements of the Recovery Package by 2020. The Recovery Package is a series of key interventions which, when delivered together, can greatly improve outcomes for people living with and beyond cancer. The package includes an holistic needs assessment, treatment summary, cancer care review, health and wellbeing clinics. These elements are part of an overall support of self-management including physical activity as part of a healthy lifestyle, managing consequences of treatment, and information, financial and work support [12]. This was upheld in the recently published NHS Long Term Plan [13]. Physical activity, is highlighted in the Recovery Package due to evidence from randomized controlled trials (RCTs) of physical activity interventions that show improvements in fatigue, pain, sleep, lymphoedema, anxiety and depression, body composition and quality of life in people living with and beyond cancer [14]. Furthermore, there is a large body of observational evidence that shows that people living with and beyond cancer who are more active have reduced all-cause and cancer-specific mortality risk and a reduced risk of cancer recurrence [15].

However, despite the guidance levels of physical activity in cancer survivors are low. For example, in one study of US prostate cancer survivors objectively measured moderate-to-vigorous physical activity was low at all 4 time points (baseline, 5 week, 6 months and 12 months; median, 0.0–5.2 min/day), with no overall change across study assessments (global P = .29) [16]. Other studies in those living with and beyond other cancers have found similarly low levels of physical activity [17]. Therefore, interventions are urgently required to promote sustainable physical activity to those living with and beyond cancer. Moreover, to our knowledge to date no physical activity intervention has been developed and implemented specifically for those living with and beyond bladder cancer. Indeed, symptoms present in bladder cancer (differentiating from other solid tumour cancers) may further discourage individuals from participation in physical activity. Specifically, frequent urination and pain. Moreover, patients with advanced bladder cancer might also have a uro-stoma that can interfere with the perceived body image.^7^

## Aim

2

The aim of the present study, financially supported by Action Bladder Cancer UK^1^, is to pilot a home-based exercise intervention tailored specifically for bladder cancer survivors (i.e. from the point of diagnosis) to improve physical and mental health outcomes (during treatment and beyond) in this population.

### Setting

2.1

King's Lynn is a hanseatic town on the coast of Norfolk in England. It has a population of approximately 49,000 residents of whom approximately 50% are male and 59% are aged between 18 and 64 years with 18% aged over 65 years. Moreover, approximately 95% of the population are white British [18]. The CADENCE Trial will be carried out initially in The Queen Elizabeth Hospital King's Lynn Foundation Trust NHS (QEHKL). Participants will be recruited from one oncology clinic at the hospital where patients are under the care of one urological consultant (co-principal investigator). The patients will be recruited from the patients with newly diagnosed bladder cancer or diagnosed with recurrence of bladder cancer at the QEHKL. They will subsequently be booked for a transurethral resection of the bladder cancer. About 20–30% of these patients will need further treatment in the form of radical cystectomy.

## Method and analyses

3

The evaluation of this pilot study will use a randomised controlled trial design. Baseline data collection will take place shortly after clinical diagnosis of bladder cancer. The duration of the entire study will be 4–5 months. Participants will be randomised by a trial coordinator (using simple random sampling) as they enter the study to either the control (usual care) or the intervention group (exercise) at baseline and prior to consent. Concealed allocation will take place. The unit of randomisation will be the participant.

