### Recruitment

3.1

Participants will be patients attending one urological consultant's oncology clinic or a flexible cystoscopy outpatient appointment and consecutively screened. If the patient meets the inclusion criteria the research team will provide them with a Participant Information Sheet and a Physical Activity Readiness Questionnaire at the point of clinical diagnosis. Approximately one week later the patient will be contacted by phone by either a trained research assistant or a member of the urological consultants care team. A one week window will be given to allow the patient time to read study material. The patient will be asked if they would like to take part in the study and if the Physical Activity Readiness Questionnaire deemed it okay for them to exercise (if exercise is not deemed acceptable the participant will not be recruited into the study). If the patient agrees to take part, an appointment will be made for them at QEHKL for consent and baseline data collection. Once recruited, patients will be randomised to usual care or exercise intervention. On arrival, for baseline data collection, and before any data is collected participants will be asked to provide written informed consent. Participants will be asked if they have any questions and will be told they can withdraw from the study at any point without giving reason and no adverse action will be taken as a result of this.

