### Measures

3.6

After randomisation a trained research assistant will collect baseline data on participants demographic data including age, sex, education, current employment status, marital status and living arrangement (who they live with), and ethnicity by way of survey. Participants’ waist circumference (WC), height and weight (to calculate body mass index) will also be recorded. As well as body fat percentage and muscle mass using bio-impedance scales. Handgrip strength will be recorded using the handheld dynamometer. Fatigue will be assessed using the 13-item fatigue subscale of the Functional Assessment of Chronic Illness Therapy-Fatigue (FACIT-F) questionnaire [20]. Sleep will be assessed using the Pittsburgh Sleep Quality Index [21], an 18-item questionnaire which assesses sleep quality and disturbances over a 1-month time interval. Quality of life will be assessed using the five-level EuroQol-5D questionnaire (EQ-5D-5L) [22]. Finally, participants will be fitted with the Actigraph accelerometer to measure free-living physical activity over 7 consecutive days. Follow-up data will be collected at 7 weeks and 14 weeks.

Patients randomised to the control comparator will receive ‘usual care’ and undergo all baseline and follow-up measures.

Levels of free-living physical activity will be assessed using the Actigraph accelerometer (GT3X) at each data collection point. The Actigraph accelerometer is a valid and reliable tool to monitor free-living physical activity and its validity and reliability has been shown in multiple populations [23]. The Actigraph GT3X is worn on a belt around the waist with the device itself positioned above the right hip either over or under clothing. We will employ a sampling frequency of 30 Hz. Service users will be asked to wear the device during waking hours every day for seven consecutive days, but not during water-based activities or sleep.

In addition to the above we will also collect data on the following variables: number of patients screened, proportion of patients enrolling, and number of patients who dropout of the study.

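### Randomisation is placed before written consent and before baseline measurement, and nothing says the arm stays hidden until both are complete

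*Protocol article*

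**What the plan says.** Three sections of the protocol article bear on the order of steps.

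- **Section 3 (Method and analyses)** places allocation "to either the control (usual care) or the intervention group (exercise) at baseline and prior to consent". A trial coordinator does it by a simple method as patients enter, and the section adds "Concealed allocation will take place".
- **Section 3.1 (Recruitment)** gives the fullest chain. Patients receive the information sheet and are telephoned about a week later. Then: "If the patient agrees to take part, an appointment will be made for them at QEHKL for consent and baseline data collection". The next step is "Once recruited, patients will be randomised to usual care or exercise intervention", followed by "On arrival, for baseline data collection, and before any data is collected participants will be asked to provide written informed consent".
- **Section 3.6 (Measures)** says "After randomisation a trained research assistant will collect baseline data". The measures are demographics, body measurements, grip strength, fatigue, sleep and quality-of-life questionnaires, and finally an accelerometer worn for seven days.

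The Abstract (Methods) says the intervention arm receives its booklet directly after baseline data collection. Section 3.7.1 defines the primary outcome as change in accelerometer-measured sedentary time, light activity and MVPA, and the secondary outcomes are also changes.

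**The concern.** Randomisation makes the arms comparable among the people randomised. Here someone can be allocated and then not attend or not sign. Section 3.1 collects no data before written consent, so such a person is a randomised participant with no measurements. If the arm is known by then, the reasons for leaving can depend on it: a patient hoping for exercise may lose interest on drawing usual care, or a reluctant patient may withdraw on drawing exercise. No analysis can recover this, because nothing was measured on those who left.

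The second route runs through the baseline itself. Grip strength depends on effort, the questionnaires are self-reported, and free-living activity can react to knowing one's arm. All are taken after allocation, and every outcome is a change from them.

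The trial is a small pilot, but section 3.8 uses it to judge promise and to inform the power calculation of the full trial, so a distorted change would be carried forward.

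**Working it through.** **1. The order of steps.** Section 3 orders randomisation against consent only (randomisation first). Section 3.6 orders it against baseline only (again first). Section 3.1 is consistent with both: phone agreement, randomisation, written consent on arrival, measurement. The sections are compatible, so this is a stated sequence and not one stray phrase, although only section 3.1 sets out the chain from phone call to consent.

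**2. How long the arm stays hidden.** Two statements offer protection. Concealed allocation is asserted in section 3, but without an end point. Concealment ordinarily protects the assignment up to enrolment, and here the assignment comes before consent. The Abstract withholds the booklet until after baseline data collection, but does not say whether that means the end of the visit or the end of the accelerometer week. If it means the visit, the exercise arm's baseline week overlaps the intervention.

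**3. Possible size of arm-dependent refusal.** The documents give no refusal rate, so there is no figure to reproduce. Section 4 only names high dropout or low uptake as a risk. The following is an illustration on assumed inputs.

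Let a fraction q of one arm leave after learning the allocation and nobody leave the other. Leavers are those lowest on a standard normal trait that has correlation ρ with the outcome. The shift in the mean of those remaining is

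shift = ρ × φ(z_q) / (1 − q), in SD of the outcome.

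| q | ρ = 0.3 | ρ = 0.5 | ρ = 0.7 |
|---|---|---|---|
| 10% | 0.058 | 0.097 | 0.136 |
| 20% | 0.105 | 0.175 | 0.245 |
| 30% | 0.149 | 0.248 | 0.348 |

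The range is about 0.06 to 0.35 SD. The sign depends on who leaves which arm.

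**4. Against the precision of the trial.** With 15 per arm (section 3.8), the standard error of a difference in means is √(2/15) = 0.37 SD. By normal approximation, a nominal two-sided 5% error becomes about 5.9% for a shift of 0.10 SD, 10.5% for 0.25 SD and 16% for 0.35 SD. Section 3.9 plans non-parametric methods, so these are indications only.

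**5. Change scores.** The table concerns the level of an outcome. For change, with equal SDs at both times, the shift is (ρ at follow-up − ρ at baseline) × φ(z_q)/(1 − q). If the two correlations are equal it is zero. If they were 0.3 and 0.5 with q = 20%, then φ(z_q)/(1 − q) = 0.105/0.3 = 0.35 and the shift is 0.2 × 0.35 = 0.07 SD.

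**6. Baseline shift.** Change is follow-up minus baseline. If knowing the arm raises the exercise arm's baseline activity by d, the between-arm difference in change falls by d. This does not cancel, and it can run against the refusal effect.

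**7. The null case.** If nobody at the consent and baseline steps knows the arm, leaving and baseline values cannot depend on it, and the expected bias by both routes is zero.

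**The case against.** The strongest reply is that bias needs someone to know the arm early, and no section says anyone does. A coordinator allocates, concealment is asserted, and the booklet comes after baseline. A coordinator who holds the arm until baseline is finished fits the text. This stands as far as it goes: a reader might infer that patients and assessors will know the arm at consent, or that concealment is useless once assignment precedes consent. The documents support neither. What they show is that the duration of concealment is not stated, under a sequence that makes the duration matter.

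Second, most refusals should come before allocation. Patients have a week to read the material, complete the readiness questionnaire and agree by phone. This stands and narrows the window, but does not close it. The consent visit is where patients are invited to ask questions and told they may withdraw.

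Third, the illustration is modest. At 0.10 SD the shift is about a quarter of the standard error (0.10/0.37 = 0.27), the larger values need refusal concentrated in the tail of the trait, and a stable difference largely cancels in change. This also stands, except that cancellation does not cover a shifted baseline.

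Fourth, the trial is an exploratory pilot with outcomes described as indicative. That lowers the stakes but does not remove them, since the results feed the full trial's planning.

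**Conclusion.** The point holds in conditional form. Randomisation is stated to precede both written consent and baseline measurement, and the protocol does not say that the arm stays hidden until both are complete. This leaves the comparison open to arm-dependent loss of people without measurements, and to baseline values influenced by the allocation.

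Whether bias will occur, and how much, cannot be read from the documents. The 0.06 to 0.35 SD range rests on assumed refusal of 10% to 30% in one arm only and correlations of 0.3 to 0.7. It is not an estimate for this trial, and it applies to levels. It would be wrong to conclude that the randomised comparison is already invalid. The case for changing the order is that the exposure is unnecessary, cannot be repaired in analysis and is cheap to remove.

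**What to change.** In sections 3, 3.1 and 3.6, set one sequence: written consent; all baseline measures, including the seven-day accelerometer week; then randomisation and release of the allocation by the trial coordinator once baseline is logged as complete. Delete the clause in section 3 that puts randomisation before consent and the one in section 3.6 that puts baseline after randomisation. Align the Abstract, which should say that the booklet follows the accelerometer week, and the Discussion (section 4), which describes implementation about one week after diagnosis. Anyone lost between the phone agreement and randomisation then counts as not enrolled.

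The cost is a protocol amendment, about one week before the allocation is released, and one further contact by phone, post or at device return. Consent and the visit measures stay in the same appointment. If the Abstract already means the end of the accelerometer week, little or no delay is added.

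If waiting for completed accelerometry before randomising is not acceptable, randomise after consent and the visit measures, state that the arm stays hidden from patient and assessor until the accelerometer week ends, and report post-randomisation losses by arm. This allows allocation at the visit, but its release still waits for the week to finish.

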### Recruitment

3.1

Participants will be patients attending one urological consultant's oncology clinic or a flexible cystoscopy outpatient appointment and consecutively screened. If the patient meets the inclusion criteria the research team will provide them with a Participant Information Sheet and a Physical Activity Readiness Questionnaire at the point of clinical diagnosis. Approximately one week later the patient will be contacted by phone by either a trained research assistant or a member of the urological consultants care team. A one week window will be given to allow the patient time to read study material. The patient will be asked if they would like to take part in the study and if the Physical Activity Readiness Questionnaire deemed it okay for them to exercise (if exercise is not deemed acceptable the participant will not be recruited into the study). If the patient agrees to take part, an appointment will be made for them at QEHKL for consent and baseline data collection. Once recruited, patients will be randomised to usual care or exercise intervention. On arrival, for baseline data collection, and before any data is collected participants will be asked to provide written informed consent. Participants will be asked if they have any questions and will be told they can withdraw from the study at any point without giving reason and no adverse action will be taken as a result of this.

### Participants inclusion/exclusion criteria

3.2

The study will be restricted to adults (age ≥18) who are able to consent for themselves (presumed from completion of the consent form) and individuals who receive a diagnosis of non-metastatic (stage I–III) bladder cancer. Patients will also be screened using the Physical Activity Readiness Questionnaire. Patients will be excluded if they are unable to provide informed consent due to severe cognitive impairment, and have metastatic disease (stage IV).

### Intervention

3.3

A self-guided printed home-based exercise booklet has been co-created for those with bladder cancer (see supplementary material). The content allows patients to achieve the World Cancer Research Foundations physical activity guidelines [1] being active every day for 30 min or more (and aiming for 10,000 steps a day) [2], getting stronger and fitter (doing strength, balance and stretching exercise twice per week and two 30 min sessions of vigorous exercise per week) [19]. The booklet was co-created through an iterative process. First, the booklet was developed and designed by a sport scientist and a urological surgeon. Next, the content of the booklet was shared with patients, health professionals (urologists, oncology physiotherapist, and personal trainers) and experts (academics) in the field, who were asked to comment on the appropriateness of the content and make suggestions for improvement. The sport scientist and the urological surgeon then utilised this feedback to improve the booklet. This process continued until all involved were happy with its content.

